After the matching process, the randomization assignment was carried out in the presence of key stakeholders including PAF, local liaison persons and village representatives, upon explaining all steps. Consent for the procedures was obtained from local government officials before the random assignment. The following steps were followed: papers with paired village names were folded and put in a bag; and two village representatives from each paired village discussed on whom to pick the paper and after the other group members verified that the names could not be seen, one paper was picked. A Kenya Shilling 10 coin was used to decide which group the picked village belonged to by flipping the coin. The village representatives had decided that the head of the coin should represent the control group, justifying that Kenyatta (1st president of Kenya) was a “controlling village” and the shield to represent the intervention group. The process of choosing the folded paper and flipping of the coin was repeated for all paired villages.

The treatment group thus consists of the target population living in the randomly assigned 12 treatment villages. *i*-PUSH roll out in the treatment villages includes training of their CHVs with the LEAP tool, who subsequently introduced the health wallet to eligible women living in the treatment villages they serve, and offer them the subsidized insurance scheme on their mobile phone. The CHVs working in the control villages (as well as the remaining non-sampled villages on the longlist) have not received training on the LEAP tool until endline, nor were women in the control villages offered the health wallet and subsidized insurance on their mobile phone.

We randomized at the village level because (1) villages are served by one CHV each, who are either trained or not trained on LEAP (hence, the LEAP intervention cannot be varied within villages); (2) to avoid contamination between households within the same villages regarding health-related knowledge and behavior; and, (3) moreover, it was deemed politically unfeasible to offer the health wallet and subsidized health insurance to some eligible households in a village but not to other eligible households in that same village. Upon roll out of the subsidized health services, eligible households were encouraged to use the services, though they were given the right to opt out at any time.

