### Sample size

Sample size calculation followed Hemming et al. [7]’s study by fixing the number of clusters per arm to be 12 clusters, and then estimated the cluster size and total sample size. In the current study, it was assumed that the *i*-PUSH program could yield an effect size of 0.4 standard deviation in terms of health care utilization with an intracluster correlation (ICC) of *ρ* = 0.014. The estimates of the ICC were derived from Geng et al. [8]’s, study conducted in Nandi County which used high-frequency data on diaries on health-seeking behaviors and financial expenditures over 1 year (October 2012–October 2013). The calculation of the ICC was based on health care utilization measured as visits to any formal health provider, unconditional on reported health symptoms. It hypothesized a confidence interval of 95%, a margin-of-error of 5%, and a power of 80%. With a cluster size per arm of 12 clusters, and a total number of women per cluster of 10, the total sample size was 120 households per arm and 240 households for the full study.

To keep sample size at par, households that dropped out of the study before the start of the intervention were replaced with new eligible households on a rolling basis for a maximum period of six months, or until the program started.

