### Data management and analysis

Trained team leaders are situated in the field to supervise real time data collection. Data quality is ensured by regular spot checks and sit-ins to approximately 5–10% of each fieldworker’s daily work to verify authenticity of the data collected. Data collection is done electronically using tablets, with spot checks for quality control. The field supervisors certify the quality of the data through editing the data before they are transferred to the database. Once the data collection is completed and synchronized in a centrally located database, all inconsistencies are resolved prior to data analysis. Data quality is checked by a qualified data management team within the affiliated research organizations. An automated routine to check on data completeness, correctness, and consistency runs on 100% of the collected data. A discrepancy report is generated to help in following upon any inconsistencies, errors or missing data with the responsible interviewer. Similarly, the quality of qualitative data will be ensured through recruitment and training of qualified field interviewers with experience in qualitative data collection. A qualified transcriber will transcribe the interviews verbatim and double coding of about 10% of the transcripts will also be done to ensure consistency in the application of the codes. Access to data is granted for all research teams in respective research organizations. Data auditing is carried out by the research team on a progressive basis on weekly basis throughout the study duration.

The final analysis will investigate the extent of contamination (e.g., whether participants who were assigned to the control group nevertheless participated in the intervention) and appropriately account for it. The final will any risks of contamination, e.g., it will exclude those participants who are randomized to the intervention but do not adhere to the intervention.

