Quantitative data will be analyzed using Stata version 14 statistical software. The first set of analysis will consist of descriptive statistics and will summarize and compare using measures of central tendency and dispersion (mean (SD), range and median). This will allow us to examine participants’ characteristics across the different sub-groups. We will first check whether the outcomes and covariates in the control group and treatment group are comparable at baseline using *t* test adjusted for clustering at the village unit for continuous variables and cluster-adjusted chi-square for binary variables. The second set of analysis will consist of assessing the causal effect of the *i*-PUSH intervention via an analysis of covariance (ANCOVA) based on intention-to-treat (ITT) analysis (all respondents who are randomized will be included in the statistical analysis and will be analyzed according to the group they were initially/originally assigned). To account for clustering of data at the village level, multi-level mixed models will be used. In addition, a generalized linear mixed model for repeated measures with random components will be used.

Based on our research questions, we will explore several additional econometric models. We will explore the impact of the *i*-PUSH program on health outcomes (healthcare utilization, health status, percentage of children who are fully immunized, etc.) and financial outcomes (percentage of women using NHIF/MTIBA to access services, percentage of people enrolled in NHIF through M-TIBA, percentage of people saving through M-TIBA, total amount saved on M-TIBA, etc.) via an analysis of covariance (ANCOVA) based on ITT analysis. Since we will have several rounds of data collection on the same respondents, we will combine all rounds of data collection (baseline and follow-up waves), and we will run an ANCOVA econometric model on a pooled panel data. More specifically, in the econometric model below, we will regress the follow-up measurement of the outcome variable (dependent variable) on the following covariates: baseline measurement (pretest measurement) and treatment group while controlling for the baseline socio-demographic characteristics such as maternal age, education, socioeconomic status (wealth quintile), crowding (persons per room), occupation, etc. The considered model is thus:
1$$ {Y}_{ij}={\alpha}_0+{\alpha}_1{X}_{ij0}+{\alpha}_2{\mathrm{Treament}}_{ij}+{e}_{ij t}, $$

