with *Y*_*ij*_, *X*_*ij*0_ the posttest and pretest/baseline measures of the outcome for the *ith* respondent from the jth cluster, respectively. Treament_*ij*_ is a dummy for being assigned to the treatment group. It takes one if the respondent belongs to the intervention cluster and zero if control. *α*_2_ is the ITT effect or the impact of the *i*-PUSH program. We will use an OLS model with standard errors clustered at the level of the community units.

In addition to pretest measures, all other baseline covariates such as age, education, socioeconomic status (wealth quintile), crowding (persons per room), and occupation, will also be included in Equation (1). Thus, in Equation (1), the treatment effect of the *i*-PSUH program *α*_2_ assesses the treatment difference on post-treatment outcome adjusted for baseline.

We will assess whether the *i*-PUSH will significantly contribute in empowering women. For self-reported surveys on women empowerment, we will construct a total score of women’s empowerment which is based on a factor analysis of the various domains on which the woman indicates that she has sole, joint, or no decision-making power within the household (for each domain, the decision-making binary indicator will be equal to 1 if the woman respondent makes the decision alone or jointly with her partner and 0 otherwise). This total score will be used as the dependent variable, and Equation (1) will be used to estimate the impact of *i*-PUSH program on women’s empowerment. Furthermore, we will follow Almås et al. (2018) to construct an alternative measure of women’s empowerment based on the decision in the empowerment game. This dependent variable will be the willingness-to-pay which is the share that the woman is willing to pay in order to receive the amount herself in private rather than giving a (higher) amount to her husband. Interim data analyses (e.g., for policy briefs) are done using baseline and weekly diaries data to inform the context and implementation of the research or *i*-PUSH program.

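### The rule excluding intervention-arm non-adherers from the final analysis conflicts with the stated ITT analysis and is not labelled as secondary

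*Protocol article*

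**What the plan says.** All the analysis statements stand in the protocol article under *Data management and analysis*.

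- **Contamination paragraph.** It opens with "The final analysis will investigate the extent of contamination", gives control participants who took part in the intervention as the example, and promises to account for this. The next sentence, which lacks words as printed, turns to contamination risks and gives as its example that "it will exclude those participants who are randomized to the intervention but do not adhere to the intervention".
- **Effect analysis, next paragraphs.** The causal effect is to be estimated by "analysis of covariance (ANCOVA) based on intention-to-treat (ITT) analysis", defined so that "all respondents who are randomized will be included in the statistical analysis and will be analyzed according to the group they were initially/originally assigned". Below Equation (1), the treatment coefficient α₂ "is the ITT effect or the impact of the" programme.

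Under *Study design and randomization procedure*, the article says that "eligible households were encouraged to use the services, though they were given the right to opt out at any time". Non-adherence in the intervention arm is therefore possible by design. The article gives no expected adherence rate and no definition of adherence for a package that combines CHV training, the health wallet, savings and insurance.

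**The concern.** An analyst who follows the contamination paragraph drops part of the intervention arm. One who follows the paragraph after it keeps everyone. The article does not rank the two rules or assign them to different analyses.

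Of the two, the exclusion is the invalid one for a causal claim. It conditions on something that happens after allocation, and it can be applied in one arm only. Control women are not offered the wallet or the subsidised insurance before endline, so control households that would have declined cannot be identified and removed to match. A selected intervention group would then be compared with an unselected control group, and the coefficient would no longer be the ITT effect that the article calls it. The primary outcome, visits to formal providers, is a behaviour that could well be related to willingness to take up a health programme.

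**Working it through.** **1. Can both statements hold?** They could if the exclusion belonged to a separate, named analysis. The article names none: the rule is attached to the final analysis, and no per-protocol or sensitivity analysis is described. As printed, the two conflict. This step needs no arithmetic.

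**2. The plan's own sample size.** Inputs from *Sample size*: effect 0.4 SD, ICC 0.014, 12 clusters per arm, 80% power, and 5% alpha (read as two-sided).

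- Individually randomised size per arm: 2 × ((1.960 + 0.842)/0.4)² = 98.1
- Cluster size with 12 clusters fixed: 98.1 × (1 − 0.014) / (12 − 98.1 × 0.014) = 9.10, rounded up to 10
- Total: 12 × 10 = 120 per arm, 240 overall, as stated
- Design effect: 1 + 9 × 0.014 = 1.126; SE = √(2 × 1.126/120) = 0.137 SD; power 83.1% (normal approximation) or 79.7% (t, 22 df)

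The stated size reproduces and is not in question.

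**3. Bias from one-arm exclusion when the programme has no effect.** Let p be the share adhering and g the difference in mean outcome, in SD, between adherers and non-adherers that would exist without any programme. The control mean is p·μ_A + (1 − p)·μ_N, and the retained intervention mean is μ_A. The difference is (1 − p)(μ_A − μ_N) = (1 − p)·g.

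With exclusion, the average intervention cluster has 10p households, so

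SE = √[1.126/120 + (1 + (10p − 1) × 0.014)/(120p)], and type I error = P(|Z + bias/SE| > 1.96).

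The article gives neither p nor g. The values below are assumptions.

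| p | g (SD) | Households left in intervention arm | Bias (SD) | SE | Type I error |
|---|---|---|---|---|---|
| 0.9 | 0.2 | 108 | 0.02 | 0.140 | 5.2% |
| 0.7 | 0.3 | 84 | 0.09 | 0.149 | 9.3% |
| 0.6 | 0.5 | 72 | 0.20 | 0.156 | 25% |

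For the middle row: bias = 0.3 × 0.3 = 0.09; SE = √(1.126/120 + 1.084/84) = 0.149; bias/SE = 0.60.

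The range runs from 0.02/0.4 = 5% to 0.20/0.4 = 50% of the planned effect. A negative g gives the same error rate with the bias reversed in sign.

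**4. Loss of precision.** Ignoring bias, power at 0.4 SD falls from 83.1% to 81.4%, 79.2% or 76.4% if 10%, 20% or 30% of the intervention arm is removed (normal approximation).

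**The case against.** The best defence is that the effect analysis is consistently ITT. The principle is stated twice, the analysis set is defined, and α₂ is called the ITT effect. The exclusion sits in one defective sentence of a data-handling paragraph, is given only as an example, and names no outcome or estimator. It may be a remnant of an intended per-protocol check. This stands as a limit on what can be said about intent. It does not remove the conflict, because the printed text attaches the rule to the final analysis without qualification.

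The size is also open to challenge. Year-one insurance is free and CHVs enrol women digitally, so adherence may be high, and at 90% with a 0.2 SD gap the inflation is negligible. Adjustment for baseline outcome, wealth, education and occupation could absorb part of any gap. Both points stand. Adjustment cannot be relied on to remove selection on unmeasured traits.

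A reader might infer more than the article supports:

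- **That a false benefit will result.** Nothing documents how decliners differ. The requirement that the mobile number be registered in the woman's own name suggests some selection, but it fixes neither direction nor size.
- **That control-arm contamination is ignored.** The sentence just before the exclusion undertakes to investigate it and account for it. That is vague, but it is there. The exclusion itself does not address that kind of contamination.
- **That replacing dropouts also breaks the ITT set.** *Sample size* says households lost before the intervention were "replaced with new eligible households on a rolling basis for a maximum period of six months, or until the program started". This permits replacement after the coin flip, but the article dates neither the flip nor any replacement and gives no number. It is a separate matter of unknown size, and it is not exclusion for non-adherence.

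**Conclusion.** The point holds as a contradiction in the text that affects who enters the main analysis. The article states a one-arm, post-randomisation exclusion for the final analysis and, beside it, an ITT analysis of everyone randomised, with nothing to make the exclusion secondary. As written, the exclusion rule is wrong and needs correcting.

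The bias it could cause has unknown direction and size. The range of 0.02–0.20 SD, with type I error of about 5–25%, rests on assumed adherence of 60–90%, an assumed gap of 0.2–0.5 SD, a normal approximation, and no baseline adjustment. It shows that the choice of rule can matter; it does not predict what will happen. Nor does the article establish that the sponsor means to base its main conclusion on adherers only.

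**What to change.** 1. Delete the exclusion from the description of the final analysis, or relabel it as a supplementary per-protocol analysis with adherence defined before outcome data are examined.
2. State once, explicitly, that the primary analysis is ITT, with all randomised respondents analysed as assigned, and repair the incomplete sentence.
3. If an estimate allowing for non-adherence or control-arm uptake is wanted, a complier-average (instrumental-variable) analysis with village assignment as the instrument may be added as supplementary only. Its assumptions should be stated. Assignment also brings LEAP-trained CHVs to the whole village, and they may affect women who never enrol. It is therefore doubtful that assignment acts only through enrolment, and such an estimate could credit the effect of the CHV training to insurance.
4. Optional and secondary: if any household was replaced after the coin flip, identify it and show a sensitivity analysis.

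Items 1 and 2 cost a wording change. All 240 households stay in, so the planned size and power do not move. Items 3 and 4 would use data from the planned collection.

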**Methods:**

This is a study protocol for a cluster randomized controlled trial (RCT) study that uses a four-pronged approach—including year-long weekly financial and health diaries interviews, baseline and endline surveys, a qualitative study, and behavioral lab-in-the-field experiments—in Kakemega County, Kenya. In total, 240 households from 24 villages in Kakamega will be followed to capture their health, health knowledge, health-seeking behavior, health expenditures, and enrolment in health insurance over time. Half of the households live in villages randomly assigned to the treatment group where *i*-PUSH will be implemented after the baseline, while the other half of the households live in control village where *i*-PUSH will not be implemented until after the endline. The study protocol was reviewed and approved by the AMREF Ethical and Scientific Review Board. Research permits were obtained from the National Commission for Science, Technology and Innovation agency of Kenya.

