### Subsidized access to NHIF SupaCover health insurance through the M-TIBA health wallet

The improved knowledge on health and health financing of women and men is also expected to translate into improved attitudes towards insurance and saving for health and insurance. To support these changes in knowledge and attitudes, WRA would receive the first year of their NHIF insurance premium at 100% subsidy and the second year at a 50% subsidy. The subsidies are expected to enhance initial enrolment in NHIF such that enrollees can experience first-hand the benefits of insurance. Moreover, this will allow women to be acquainted with regular savings for the insurance premium for the next year, such that they will get into the habit of recurrent savings and increasingly be able to frequently set aside small amounts of money.

An integral component of the *i*-PUSH program is the so-called “health wallet” on M-TIBA (a mobile payment platform). Most WRA in the target population have limited access to formal financial services such as bank savings accounts. The widespread availability of M-PESA opens a new avenue of change in this respect. To alleviate this constraint, *i*-PUSH offers women the opportunity to set aside money in a commitment savings device on their mobile phone. The only requirement is that the mobile number is registered on their personal name. This will allow them (and other people such as spouses, relatives) to transfer funds into the wallet through M-PESA, which are subsequently “reserved” for direct payment of medical costs at M-TIBA-connected health providers or for future payment of the annual insurance co-premium. This feature of the health wallet is expected to support women in their financial planning—funds transferred into the wallet are kept safe and secure until they are needed for health-related purposes. Additional small-scale interventions are added to the program to enhance further savings, such as the provision of a savings calendar. Thus, this component of the program expects to increase savings for health as well as uptake and renewal of health insurance among the target population.

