### Financial and health diaries

This study uses weekly financial and health diaries data collection methodology as its core research instrument, because this technique is well suited to address the research objectives by providing a granular insight into the financial lives and health-related decisions of participating households. The diaries are collected over the full study period between baseline and endline survey. The financial diaries record all financial transactions such as purchases, gifts, remittances, and loans, including those between household members in the 7 days prior to each interview. Transactions are described by type, incoming or outgoing cash, amount, purpose, transaction partner, and date. The health diaries provide a detailed picture of the incidence of illnesses and injuries, as well as preventive and curative health-seeking behavior. Health diaries collect data on all health events that occurred to any of the household members (respondents, their children and other household members) in the 7 days prior to each interview. This includes symptoms, whether any health care was sought, which health provider was visited, health services received, out-of-pocket health expenditures, date of onset of the symptoms, and date of provider visit(s).

Respondents to the weekly diaries interviews are all adults in the study households who are economically active (i.e., who handle money, excluding young adults who are still studying) and capable of conducting the interview (i.e., excluding very old-age or disabled household members). Emancipated minors, i.e., teenage girls who are a mother or who are pregnant, are also included as diaries respondent. The financial diaries are reported by each individual him- or herself. The health diaries can be reported by one individual for the entire household.

Data are collected through structured and formatted digital tools that allow to analyze data as they are recorded and improve data collection tools mid-course of the process. The short recall period drastically reduces recall bias and ensures that both major and minor illness episodes, including those with foregone care are reported. Because interviewers visit households weekly, they build a relationship of trust, which enables the diaries to capture also more sensitive health events. This is of particular importance in relation to capturing maternal and child health experiences.

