## Conclusions

This study aims to evaluate the impact of *i*-PUSH program on maternal and child health care utilization, women’s health including their knowledge, behavior, and uptake of respective services, as well as women’s empowerment and financial protection. It also aims to evaluate the impact of the LEAP training tool on empowering and enhancing CHVs’ health literacy and to evaluate the impact of the M-TIBA health wallet on savings for health and health insurance uptake. The findings will inform stakeholders to formulate better strategies to ensure access to UHC in general and for those highly vulnerable segments of the population in particular. The findings of this research will provide valuable information on UHC policies for the academic community, policy-makers, and other stakeholders to support the achievement of SDGs.

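### Three of the four named savings and insurance outcomes count only the M-TIBA channel, which control villages were not offered, so their intention-to-treat coefficient mainly restates uptake; no any-route outcome is named for the stated aim

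*Protocol article*

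**What the plan says.** The aim is given in the abstract and repeated in the Conclusions: to "evaluate the impact of the M-TIBA health wallet on savings for health and health insurance uptake". The section on subsidized access to NHIF SupaCover states the expected effect just as broadly: "this component of the program expects to increase savings for health as well as uptake and renewal of health insurance among the target population".

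The section on data management and analysis names four financial outcomes for an ANCOVA by intention to treat. The first is "percentage of women using NHIF/MTIBA to access services". The other three are "percentage of people enrolled in NHIF through M-TIBA, percentage of people saving through M-TIBA, total amount saved on M-TIBA". The list is left open at its end. The same section says of the treatment coefficient that it "is the ITT effect or the impact of the" *i*-PUSH programme.

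On the control arm, the section on study design and randomization says that its volunteers were not trained on LEAP before endline, "nor were women in the control villages offered the health wallet and subsidized insurance on their mobile phone".

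The primary and secondary outcome lists contain no savings or insurance outcome. The analysis section is therefore the only place where this aim is given one.

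**The concern.** An outcome that counts only what passes through the intervention's own channel should be close to zero in the control arm by design. The between-arm difference is then the treated-arm level of wallet use under another name. It says that the programme was taken up. It does not say whether more women became insured, or whether more money was set aside for health, than without the programme.

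Switching is plausible on the protocol's own account:

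- The first-year premium is free and the endline survey falls about one year after introduction. A woman who would have joined NHIF through the insurance office therefore has a reason to join through the wallet instead.
- The wallet is filled by M-PESA transfer, so money already held elsewhere for health can be moved into it.

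If the coefficient is reported as programme impact, any such switching is reported as gain. The stated aim on savings and insurance is then left without an outcome that answers it.

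**Working it through.** **The plan's own figure.** The protocol gives no calculation for these outcomes. Its only computed figure is the sample size, which concerns health care utilization. It reproduces:

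- Unclustered n per arm for 0.4 SD, two-sided 5%, 80% power: 98.1.
- Cluster size with 12 clusters per arm and ICC 0.014: 98.1 × 0.986 / (12 − 98.1 × 0.014) = 9.10, rounded up to 10.
- Total: 24 × 10 = 240.

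Nothing below depends on it.

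**Inputs for enrolment.**

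- u, enrolment through M-TIBA in treated villages: 40%, an assumption.
- M-TIBA enrolment in control villages: 0, because the wallet was not offered there. If contamination made it k, the difference would be u − k, which still does not involve switching.
- c, coverage that would exist without the programme: 8% to 20%, the national figures for 2009 and 2014 in the Discussions. The same paragraph says that poor, rural and informally employed people are less often insured, so c is probably lower here.
- s, the share of c that switches to the M-TIBA route: 0 to 1, unknown.

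**Formulas.**

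- M-TIBA-only difference: u − 0 = u, whatever s is.
- Any-route difference: [u + c(1 − s)] − c = u − c·s.

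| c | s | M-TIBA-only difference | Any-route difference |
|---|---|---|---|
| 8% | 0 | 40 points | 40 points |
| 8% | 0.5 | 40 points | 40 − 4 = 36 points |
| 8% | 1 | 40 points | 40 − 8 = 32 points |
| 20% | 0 | 40 points | 40 points |
| 20% | 0.5 | 40 points | 40 − 10 = 30 points |
| 20% | 1 | 40 points | 40 − 20 = 20 points |

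**Savings.** Let A be the mean amount on M-TIBA in the treated arm, and d the share of it that was already set aside for health elsewhere. The M-TIBA difference is A. The net gain in savings for health is A(1 − d). For A = 100 units the outcome shows 100 in every case, while the net gain is 100, 50 or 0 for d = 0, 0.5 or 1. Money moved in from general savings has d = 0, because the wallet reserves it for health.

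**Baseline term.** Before roll-out, the M-TIBA measures should also be near zero in both arms. This is an inference, not a statement in the protocol. If it holds, the baseline covariate in the ANCOVA carries almost no information for these outcomes.

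**Data for any-route outcomes.** The abstract says that all households are followed for "health expenditures, and enrolment in health insurance over time", with no restriction on route. On transactions: "The financial diaries record all financial transactions such as purchases, gifts, remittances, and loans". The survey modules on savings groups and financial instruments go to all adults. All of this is collected in both arms.

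**The case against.** The strongest reply is that the list is illustrative. It is introduced as exploratory and left open at its end. Its first item, use of NHIF or M-TIBA, may include NHIF outside the wallet. None of these outcomes is primary or secondary, financial protection has a channel-neutral secondary outcome in out-of-pocket expenditure, and exact definitions may sit in an analysis plan that is not shown. This stands as a limit on weight. It does not remove the point. The first item measures service use, not enrolment or saving. An open list commits to nothing, and the three enrolment and savings outcomes that are named do not fit the aim.

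Four stronger readings are tempting, and the documents do not support them:

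- *The trial cannot show a net gain.* This is true of the three named outcomes, not of the data, which could support any-route measures.
- *Any uptake at all will give a significant result.* It will not. With 3 of 120 treated women, one in each of three villages, against none in control, the village proportions have mean 0.025. Their variance is (3 × 0.075² + 9 × 0.025²)/11 = 0.00205, so the standard error is √(0.00205/12) = 0.0131. Then t is about 1.9 on 22 df, short of the 5% level.
- *All money moved into the wallet is displacement.* The aim concerns savings for health, so only money already earmarked for health counts as displaced.
- *The between-arm M-TIBA contrast should be dropped.* The protocol plans to examine contamination, and that contrast is needed for it. Control use may also not be exactly zero, since *i*-PUSH has run in parts of the county since 2017.

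**Conclusion.** The point holds for the three M-TIBA-specific outcomes. Their intention-to-treat coefficient mainly restates treated-arm uptake and is insensitive to switching, yet the protocol reads it as the impact of the programme. No any-route outcome is named for the aim on savings and insurance.

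In the illustration, the overstatement of the coverage gain runs from nil to 8 points at 8% otherwise-existing coverage, and from nil to 20 points at 20%, against 40 points shown. The upper end is an extreme: it needs this low-income rural sample to match the national average and every otherwise-insured woman to switch. The 40% uptake and the switching shares are assumptions. For savings, the size depends on how much wallet money was already held for health, on which the protocol gives no figure.

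This is a mismatch between outcome and aim in an exploratory part of the analysis. It does not touch the primary outcome or the sample size, but it should be corrected before results on savings and insurance are described as impact.

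**What to change.** Name two intention-to-treat impact outcomes, measured the same way in both arms:

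- (a) enrolment in NHIF or any other health insurance, by any route;
- (b) where the diaries and the savings-group and financial-instrument modules allow it, the amount set aside for health or insurance across all channels, including the wallet.

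Keep the M-TIBA-specific measures and their between-arm contrast, but describe them as uptake and contamination indicators, not as programme impact. State whether the item on use of NHIF or M-TIBA includes NHIF obtained outside the wallet.

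The cost is mainly definition work. The sample size does not change, and outcome (a) rests on information already planned in both arms. The any-route effects will be smaller and noisier than the M-TIBA figures. Outcome (b) may be measured imperfectly: earmarking for health is documented only for the wallet, and cash kept at home need not appear as a transaction.
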